#### Effect evaluation

The outcomes of the questionnaires will be compared between both groups at the three different measurements. Descriptive statistics will be used to summarise the data and detect outliers, missing values and data entry mistakes. We will describe the categorical variables using frequency tables; for each continuous variable we will calculate minimum, maximum, range, median, mean and standard deviation. The data will be further analysed using a multi level model to assess the influence of the different variables. All analyses will be performed at patient level according to the intention to treat principle, so patients will be regarded as belonging to the intervention group if their GP was allocated to the intervention condition, regardless of whether the GP effectively received the training.

The primary independent variable in the analyses will be the GPs’ exposure to the training: trained GP or control group delivering usual care. The primary dependent variables are their patients’ score on the RTW-SE scale, the number of Z05 codes used by the GPs and the proportion of working age patients for whom the occupation is registered. Effects of the intervention will be checked for effect modification by experience and gender of the GPs. All analyses will be performed with SPSS. Effects on the different outcome variables will be assessed at a significance level of 0.05.

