### Procedures

Inclusion will take place during a 4 month period, starting after the training of the intervention group GPs. The GPs’ receptionists will approach patients in the waiting room with a short questionnaire about age, number of working hours and their willingness to participate in the project. If a patient meets the selection criteria and signs informed consent the patient will be included and receive the first questionnaire. A second and third questionnaire will follow after 6 and 12 months. Forty patients for each participating GP, 20 females and 20 males, will be included for the study.

Only the intervention group GPs will be asked to fill in a form for each consenting patient with questions about: 1 the occupation of the patient; 2 the work relatedness of the problem that he/she presented; 3 whether sick leave was discussed; 4 whether the GP had suggested contacting an OP; 5 whether the GP had stimulated the patient to adopt a pro-active coping style. Two final questions asked whether the GP thought the training had been helpful for the consultation and if the GP had enough time for the consultation.

The control group will deliver care as usual. As it could be surmised that their usual care is influenced by the data collection we try to make sure that the data collection in the control group practices is carried out as much as possible by the receptionists supported by a research assistant. When data collection is completed the control group GPs are offered the same training as the intervention group as an incentive for adherence to the study protocol.

Patients will be approached by the receptionist before the consultation and, if they are prepared to participate in the study, are asked to answer the first questionnaire after the consultation and a second and third questionnaire after six and twelve months respectively.

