#### Secondary outcome measures

The secondary outcome measure at GP level is GP’s attention for the patients’ work related problems as it is perceived by patients. It is measured by a self-constructed five item scale, with 2 response categories: “yes” or “no” concerning: 1. Does the GP know your occupation? 2. Do you think the problem for which you consulted the GP is work related? 3. Was this possible relationship discussed by your GP? 4. Did your GP discuss sick leave? 5. Did the GP help you to find solutions for work-related problems?

As mentioned above, intervention group GPs are asked to fill in a form for each participating patient with questions on the same topics. This will provide us with information about the extent to which intervention group GPs and patients agree on these issues.

Secondary outcome measures at patient level consist of productivity, sick leave duration, health related to work, quality of life, self-rated health and direct illness-related costs, health care and non-health care. Measures for productivity are both absenteeism and presenteeism. Absenteeism refers to the total days lost from work. Presenteeism refers to attending work whilst still sick or disabled, causing reduced productivity while at work [22,24,25]. Sick leave and presenteeism will be measured with modules C and D of the Productivity and Disease Questionnaire (Prodisq) [26]. The Prodisq is developed based on the Quantity and Quality (QQ) method and provides a reliable and valid tool for measuring quantity and quality of work on a daily basis [25,26]. Quality of life will be measured by means of the RAND-36 and EQ-5D-5 L [27,28]. The RAND-36 consists of 8 subscales: physical functioning, role limitations due to physical problems, social functioning, bodily pain, general mental health, role limitations due to emotional problems, vitality, and general health perceptions [28]. The EQ-5D-5 L is an improved version of the Euroqol (EQ-5D). In contrast to the Euroqol, the EQ-5D-5 L has 5 levels of severity in 5 dimensions, instead of 3 levels of severity in 5 dimensions, which improves the instrument’s sensitivity [28].

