Self-rated health will be assessed using one item from the Short Form Health Survey (SF-36). This widely used measurement tool describes how a respondent values and assesses his/her general health [29]. To detect health complaints and co-morbidity underlying work disability, questions derived from The Netherlands Working Conditions Survey (NWCS) will be used [30].

Direct costs, both healthcare and non-healthcare, will be measured by an adapted version of the Trimbos/iMTA questionnaire (TiC-P) [31].

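### For recalled days lost, sick leave and costs, the first questionnaire looks mainly backward, yet the plan makes it one of three between-arm comparisons and gives it no baseline role

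*Protocol article*

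**What the plan says.** **Timing (Procedures).** "Inclusion will take place during a 4 month period, starting after the training of the intervention group GPs". Patients are approached before the consultation and "are asked to answer the first questionnaire after the consultation and a second and third questionnaire after six and twelve months respectively".

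**Outcomes (Secondary outcome measures).** The patient-level list includes productivity, sick leave duration and direct costs inside and outside health care. "Absenteeism refers to the total days lost from work". Sick leave and presenteeism come from two Prodisq modules, and direct costs from an adapted TiC-P. The article gives no recall period for either instrument.

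**Analysis (Effect evaluation).** "The outcomes of the questionnaires will be compared between both groups at the three different measurements". Descriptive statistics follow, and then: "The data will be further analysed using a multi level model to assess the influence of the different variables". The section ends: "Effects on the different outcome variables will be assessed at a significance level of 0.05". No measurement is called a baseline, and outcomes built on recall are not separated from outcomes that describe the patient's state at completion.

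**The concern.** The plan applies one comparison rule to two kinds of quantity. RTW-SE and the patient's view of the GP's attention to work can properly be read as outcomes straight after a consultation with a trained or untrained GP. Days lost, sick leave duration and costs build up over past time. Reported just after the index consultation, they describe a period that this consultation could hardly have changed.

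Two things are at stake.

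- **Interpretation.** Recruitment follows allocation and training. An arm difference in recalled absence or cost at the first questionnaire would mainly show that the two sets of practices enrolled different patients. Under Strengths and weaknesses, the article assumes that patient selection works alike in both arms. These values could check that assumption, but the plan lists them as an outcome comparison.
- **Estimation.** If the first occasion shares one group effect with the other two, it pulls the estimate towards zero. As a covariate, the same value would instead correct for imbalance in prior absence and cost.

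**Working it through.** **Inputs from the article.** Questionnaires after the consultation and at 6 and 12 months; inclusion over 4 months, starting after training (Procedures). SD 1.14, difference of half an SD, ICC 0.15, 30 analysed patients per GP, 12 GPs per arm, 80% power, alpha 0.05 (Sample size).

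**Assumed, because not stated.** Recall of 1, 3 or 6 months; inclusion spread evenly from the time of training; correlation r between occasions of 0.3 or 0.5; ICC 0.15 borrowed from RTW-SE.

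**1. The plan's own figure.** The article gives no figure on this point. Its sample size, which supplies the cluster inputs, reproduces (two-sided alpha):
- 63 patients per arm for 0.57/1.14 = 0.5 SD without clustering.
- Design effect 1 + 29 × 0.15 = 5.35.
- 63 × 5.35 = 337 patients per arm; 337/30 = 11.2, so 12 GPs.
- 30/0.75 = 40 recruited per GP.

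The point concerns secondary outcomes only and changes none of this.

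**2. How much of the recall period precedes training.** A patient included t months after training, with recall R, has a share max(0, R − t)/R before training. Averaged over t from 0 to 4:
- R = 1: 1/8 = 12.5%
- R = 3: 3/8 = 37.5%
- R = 6: 1 − 2/6 = 66.7%

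So 87.5%, 62.5% or 33.3% falls after training. The period is largely before the index consultation but not wholly before the intervention.

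**3. Dilution, if one group effect is averaged over three equally weighted occasions.** Let the effect be δ at 6 and 12 months and fδ at the first questionnaire. The average is (f + 1 + 1)δ/3.
- f = 0: 2δ/3 = 0.67δ
- f = 0.25 (illustrative, for patients who had already seen the trained GP): 0.75δ

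With an arm-by-time term, or with separate comparisons at each occasion, the estimates at 6 and 12 months are not diluted.

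**4. Precision from adjustment, patient-level variance only.** With equal variances and correlations, the mean of the two follow-ups has variance (1 + r)/2. Adjusting for the first value removes r².
- r = 0.3: 0.09/0.65 = 13.8%
- r = 0.5: 0.25/0.75 = 33.3%

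**5. The same gain with clustering.** The variance of a GP mean, in SD² units, is 0.15 + 0.85/30 = 0.150 + 0.028 = 0.178. The patient-level part is 0.028/0.178 = 16%, and the rest (84%) lies between GPs. If adjustment acts only on the patient-level part, total variance falls by:
- r = 0.3: 13.8% × 0.16 = about 2%
- r = 0.5: 33.3% × 0.16 = about 5%

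If the covariate explains the same share of the between-GP variance, the full 14% or 33% applies.

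**The case against.** Five counter-arguments deserve a fair statement.

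- **Comparing is not testing.** A reader might infer that the arms will be tested at 0.05 on prior sick leave as an intervention result. The text does not say so. The comparison sentence is followed by descriptive statistics, and the 0.05 sentence speaks of effects without assigning a test to the first questionnaire. This stands.
- **Model terms may sit in a fuller plan.** Baseline covariates are commonly left to an analysis plan, and none is shown. This would dispose of a complaint about silence. But the article does state a rule, comparison at all three measurements without distinction, and that rule fits the recall-based outcomes badly.
- **Wholly before the consultation is an inference.** No recall window and no delay to completion are given, and the consultation itself may fall inside the window. Largely before is what the timing supports. Presenteeism is left out of this point, because the article describes the Prodisq as measuring work on a daily basis.
- **Before the consultation is not before the intervention.** This stands. A patient may already have seen the trained GP, so the covariate may be partly exposed and the first-occasion effect need not be zero.
- **The size is easily overstated.** A reader might turn the 2/3 shrinkage into a large loss of power. That needs a pooled model that the article does not specify, and it ignores between-GP variance. No power figure is claimed here.

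A reader might also suppose that first-questionnaire costs will be added into the follow-up totals. Nothing in the article says this, and it refers the economic methods to a separate publication.

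**Conclusion.** The point holds in limited form. For days lost, sick leave duration, absence-related productivity loss and costs, the stated rule treats a largely pre-consultation period as one of three outcome occasions and leaves a useful baseline value without a role. Because patients enter after allocation, an arm difference there would mainly reflect recruitment.

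The size is conditional. Shrinkage to about 2/3 arises only with a single group effect over three equally weighted occasions and no effect at the first. The gain from adjustment runs from about 2% to 14% of total variance at r = 0.3, and from about 5% to 33% at r = 0.5, depending on whether the covariate also explains between-GP variance. Both correlations, and the ICC for these outcomes, are assumptions. The stronger case for the change is correction of recruitment imbalance and clear interpretation. RTW-SE, perceived GP attention, the GP-level primary outcomes and the sample size are unaffected.

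**What to change.** In Effect evaluation, for days lost, sick leave duration, absence-related productivity loss, health care costs and non-health care costs:

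1. State the recall period of each item.
2. Estimate intervention effects at 6 and 12 months from the multilevel model, with the patient's own first-questionnaire value as a covariate.
3. Report the first-questionnaire values by arm descriptively, as a check on recruitment imbalance.
4. Add an unadjusted sensitivity analysis at 6 and 12 months, because the covariate is measured after allocation and may be partly exposed.

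Keep RTW-SE and perceived GP attention as post-consultation outcomes at the first questionnaire.

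The cost is wording and one extra analysis per outcome; no new data are needed. The small downside is the possibly exposed covariate, which the sensitivity analysis is there to reveal.

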### Participants

#### General practitioners

GPs working in the South-Eastern part of the Netherlands will be asked by letter to participate in the study. If an insufficient number of GPs respond positively to the letter, GPs will be approached more directly by email and telephone. Only GPs who work at least 2 days per week will be recruited.

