### Outcome measures

#### Primary outcome measures

As primary outcome measures at GP level we use the registration of patients’ employment in the electronic medical record (EMR) and the use GPs make of the code Z05 (for work related problems) of the International Classification of Primary Care (ICPC). For each participating GP we establish the percentage of the working age patients for whom the occupation is recorded anywhere in the EMR and we count the instances in which they made use of code Z05. The registration of employment and use of code Z05 in the 6 months following the training will be compared between intervention and control group practices.

The primary outcome measure at patient level is the work-related self-efficacy, measured by the 11 item Return-to-Work Self-Efficacy scale ( RTW-SE) [22]. This scale measures the extent to which people feel able to handle the demands of their job on a scale which ranges from 1 to 6. The RTW-SE is validated and reliable and has a high internal consistency. It was found to strongly correlate to return to work in a sample of sick listed workers; it was also shown to be sensitive to changes in the clinical condition of patients suffering from mental health problems [23].

Outcome measures regarding gender are the use of code Z05 and the registration of occupation in women and men. Moreover we will analyse the score on the RTW-SE scale and investigate its relation to gender and how this is modified by other patient variables like age, occupation, income, health problems, absenteeism and other patient variables.

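### Z05 use, a primary outcome, is a raw count per GP with no denominator, and the statement that all analyses are at patient level does not fit it

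*Protocol article*

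**What the plan says.** The protocol article (Primary outcome measures) separates GP-level from patient-level primary outcomes. The GP-level pair opens with "As primary outcome measures at GP level we use the registration of" employment, and Z05 use is the second of the pair. Their definitions differ in form:

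- Occupation: "For each participating GP we establish the percentage of the working age patients for whom the occupation is recorded anywhere in the EMR". This has a denominator.
- Z05: "we count the instances in which they made use of code Z05". This has none.

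The period is common to both arms: "The registration of employment and use of code Z05 in the 6 months following the training will be compared between intervention and control group practices".

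Under Effect evaluation, the dependent variables for these outcomes are "the number of Z05 codes used by the GPs and the proportion of working age patients for whom the occupation is registered", so the contrast between a number and a proportion is repeated. The preceding paragraph says "The data will be further analysed using a multi level model to assess the influence of the different variables" and then "All analyses will be performed at patient level according to the intention to treat principle".

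On GP eligibility, the plan says "Only GPs who work at least 2 days per week will be recruited". It gives no upper limit.

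**The concern.** A six-month window equalises calendar time but not opportunity. A GP with more working days, a longer list or more consultations can record more Z05 codes while having the same tendency to use the code. The raw count mixes that tendency, which the training is meant to change, with workload, which it is not. With about 12 GPs per arm, this adds noise to a comparison that has little information to spare, and the result (so many more codes per GP) cannot be read as a change in behaviour without knowing the workload behind it.

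The level of analysis adds an ambiguity. Z05 use has no patient-level definition anywhere in the article, yet every analysis is said to be at patient level. An analyst following the text has no stated way to model this primary outcome.

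**Working it through.** **1. The plan's own figure.** The sample size section gives SD 1.14, a difference of half an SD (0.57), power 80%, alpha 0.05 (taken as two-sided), 30 analysed patients per GP and ICC 0.15.

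- Per arm without clustering: 2 × [1.14 × (1.960 + 0.842) / 0.57]² = 62.8, so 63.
- Design effect: 1 + 29 × 0.15 = 5.35.
- GPs per arm: 63 × 5.35 / 30 = 337.05 / 30 = 11.2, so 12. Recruitment: 30 / 0.75 = 40.

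The figure reproduces. It concerns the self-efficacy scale only, and the present point leaves it unchanged.

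**2. Information available for Z05.** One count per GP gives 12 v 12 values. The smallest difference detectable with 80% power is (1.960 + 0.842) × √(2/12) = 1.14 between-GP SDs, or 1.20 with the t distribution on 22 df. Avoidable between-GP variation therefore matters.

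**3. What the missing denominator adds.** Inputs assumed here and not given in the article:

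- working days of 2, 3, 4 or 5 a week, equally likely (the lower limit is the plan's, the upper limit is not);
- codes proportional to days;
- between-GP coefficient of variation (CV) of the underlying rate 0.5;
- a control mean of 10 or 2 codes per GP;
- no practice clustering.

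The CV of days is 0.319, squared 0.102. With days scaled to mean 1, the mean of 1/days is 3.5 × (1/2 + 1/3 + 1/4 + 1/5) / 4 = 1.123. For control mean m:

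- CV² of the count = 1/m + (1.102 × 1.25 − 1) = 1/m + 0.378
- CV² of the rate = 1.123/m + 0.25

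| m | CV, raw count | CV, rate |
|---|---|---|
| 10 | √0.478 = 0.69 | √0.362 = 0.60 |
| 2 | √0.878 = 0.94 | √0.811 = 0.90 |

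The denominator helps most when codes are fairly frequent. At 2 codes per GP, Poisson noise dominates and the gain is small.

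**4. Power.** Simulation under these inputs (gamma-Poisson counts, 20,000 trials per setting, t-test on the count or on the count per unit of working time):

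| Codes per control GP | True rate ratio | Raw count | Rate |
|---|---|---|---|
| 10 | 2 | 65% | 78% |
| 2 | 2 | 45% | 50% |
| 10 | 1 | 5.0% | 4.8% |
| 2 | 1 | 4.8% | 5.0% |

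Repeat runs gave 43% to 45% v 49% to 50% in the second row. The last two rows show that type I error is about 5% for both methods.

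**5. Imbalance between arms.** Two individual GPs could differ by 5/2 = 2.5-fold under the assumed five-day maximum. Arm means differ much less: over random allocations, the ratio of mean working days has a 95% range of about 0.77 to 1.30. It departs from equality by more than 10% in about 46% of allocations and by more than 20% in about 16%.

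**The case against.** The strongest reply is that the patient-level statement is loose wording. The paragraph opens with the questionnaire outcomes, the sentence goes on to explain intention to treat for patients, and the article elsewhere labels both record-based outcomes as GP level. That reading is plausible, but the text says all analyses, and nothing in the section assigns Z05 another level. The mismatch stands as a point of wording.

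Offsets, distributions and random-effect levels are usually left to an analysis plan. That is correct, and their absence is not the point here. The outcome itself is fixed as a number without a denominator, consistently in two sections.

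Three stronger readings are tempting and are not supported:

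- *That GP values would be repeated over patients, so that 24 values pass for 24 × 30 = 720.* The plan states a multilevel model. A value identical for all patients of a GP has an intracluster correlation of 1, a design effect of 1 + 29 × 1 = 30, and an effective sample of 720 / 30 = 24. Precision would be overstated only if clustering were ignored, which the plan does not propose.
- *That both record-based outcomes are affected.* Occupation registration has a denominator and can validly be analysed as yes or no per working-age patient in a multilevel model. Without patient covariates this is equivalent to a binomial model on each GP's counts. The defect is confined to Z05.
- *That workload differences bias the comparison.* Practices are randomised, so imbalance in workload is chance, and the test allows for it.

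**Conclusion.** The point holds for Z05 use alone. Its definition as a raw count per GP leaves workload in the outcome, and the stated patient level does not fit it. The loss is in precision and interpretability, not validity.

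The size is uncertain. Under the assumptions above, the loss of power is about 13 percentage points at 10 codes per GP and about 6 at 2 codes. The article gives no expected Z05 frequency, and it remarks that even motivated GPs often do not know the relevant codes, so low counts are possible and the loss may lie at the smaller end. It would also shrink if working time varied less, or if codes rose less than in proportion to it. A change is still worth making, because this is a primary outcome and the better analysis is nearly free.

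**What to change.** Define Z05 use as a rate and analyse it at GP level within practices. Use a negative binomial or overdispersed Poisson model with the log of listed working-age patients, or of their consultations, as offset, with allowance for practice clustering. Report a rate ratio with its confidence interval. Choose the denominator before the data are seen. List size at the start of the window has the advantage that the training cannot alter it, whereas consultations follow workload more closely.

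Limit the patient-level statement to the questionnaire outcomes and, if wished, to occupation registration as a yes/no outcome per working-age patient with GP and practice random effects. The intention-to-treat rule can stay as it is.

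The cost is a few lines of wording and at most one further denominator from the record extract. The working-age list is already needed for the occupation percentage. Since Z05 use is also to be examined in women and men, the denominator should be extracted by patient sex. Design, recruitment and sample size do not change.
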